### Recruitment

All potential key informants are referred to the study by the nurse in charge at each study site. Study staff meets with all potential key informant participants (healthcare providers and caregivers) in a private area to provide further information about the study using a standardized script, assess eligibility, and obtain written informed consent. The study was deemed eligible for waiver of individual consent for index cases and their child contacts (see “Ethics and consent process”). Thus, there is no active recruitment of index cases and their child contacts in this implementation science study as the focus is on medical record review.

Phase I: pre-intervention – healthcare providers: convenience sampling was utilized, with the following recruitment targets: (1) at least one nurse per CBI site; (2) at least one LVHW from a total of three CBI sites.

Phase III: post intervention – healthcare providers: interviews commenced after the intervention has been implemented for at least one year. Convenience sampling is utilized to enroll 15–30 healthcare providers, with the following recruitment targets: (1) at least one nurse per CBI site; (2) at least one LVHW per CBI site.; and (3) at least one community-based VHW per CBI site. On average, five nurses and one to two LVHWs are employed at each site, and additional community-based VHWs are associated with each site. A sample size of 15–30 healthcare providers should enable us to reach data saturation.

Phase III: post intervention – caregivers: heterogeneous purposive sampling [37, 38] is utilized to enroll 30 caregivers according to the following recruitment targets: (1) 80% of caregivers who brought their children for TB screening, and 20% of caregivers who did not bring their children for TB screening; and (2) a proportional number of participants at each CBI site, based on patient intake. In addition, we will try to include caregivers whose children may have struggled with adherence issues. This target sample size will be augmented if we find that data saturation has not been reached based on analyses of the transcripts.

Interviews with caregivers who did not bring their children for TB screening will be conducted after cessation of intervention activities. Based on our prior experience, conducting in-depth interviews with patients (caregivers in this case) who refuse or delay recommended guidelines will be challenging. However, caregivers who did not bring their children for TB screening represent a very important group for targeted TB prevention. We will utilize our community-based VHW to explain that sharing their opinions and perspectives on declining TB screening for their child contacts is of utmost importance so that the MOH can design more appropriate future interventions. In-depth interviews will not be conducted in the community; caregivers will be compensated for their travel costs to the health facility.

### Data collection

Multiple data collection methods are utilized and include: (1) abstraction of quantitative outcome data from clinic records; (2) in-depth qualitative healthcare provider and caregiver interviews; and (3) documentation of process data through facility characteristics surveys and intervention utilization logs.

#### Quantitative data

Individual patient-level data will be collected from medical records using a standardized data abstraction tool. Information collected will include demographic and treatment information on all index cases and child contacts identified and screened for TB, diagnosis of TB and treatment initiated, IPT initiation, IPT completion, and HIV testing.

#### Qualitative data

Open-ended interview guides are used to stimulate discussion with key informants. Organizations with prior experience in translating health and technical information will translate study consent forms and post-intervention interview guides from English into Sesotho. Back-translation from Sesotho into English will be performed to verify translation accuracy and to ensure fidelity to the questions’ original intent.

Phase I interviews were conducted by a trained, experienced, qualitative interviewer with clinic nurses and the LVHW at each CBI site in a private space on-site prior to the start of the intervention; these data were used to modify the intervention. The interview guide consisted of open-ended, exploratory questions that were asked in a non-judgmental and culturally sensitive way to capture emic perspectives. Respect for participants’ privacy and confidentiality was emphasized in group interviews, and divergent perspectives were encouraged.

After intervention implementation for at least one year, additional healthcare provider interviews with nurses and LVHWs, and caregiver interviews are conducted by the same qualitative interviewer to evaluate acceptability and utilization of intervention components and the combination strategy. The Principal Investigator (PI) closely supervises the interviewer and provides timely feedback, particularly regarding probing, not asking leading questions or responding to participants in leading ways, and maintaining affective neutrality in facial expressions and body language.

#### Process data

A structured survey of facility characteristics (e.g., number of providers, stock-outs of medical and laboratory supplies, availability of laboratory services, counseling, clinical algorithms, educational materials) was conducted by the study nurse mentor with the nurse in charge at each facility prior to intervention implementation and is administered quarterly thereafter at all 10 participating health facilities. The survey documents baseline characteristics at each facility and monitors changes in intervention implementation over time. Additionally, at each CBI site, the LVHW completes an intervention log that tracks delivery of SMS messages and education sessions to document the dosage of intervention components received by each patient; the nurse mentor completes mentoring logs that assess intervention quality [33].

### Data management

Data on patients with TB and their child contacts are collected and entered directly on a dedicated study tablet, using a unique study identification number, which is stored in a secure double-locked filing cabinet at the study office. The study database is encrypted and password-protected. Established quality control measures such as skip patterns, range limitations, and consistency checks are incorporated into the database to enhance the accuracy and completeness of the data collected. The database is backed up nightly to an encrypted external hard drive maintained in a locked filing cabinet. Each key informant interview is digitally audio-recorded, transcribed verbatim, and translated to English, if necessary.

### Statistical methods

Phase I: grounded theory methods were used to analyze data from Phase I, a pre-intervention exploratory phase that allowed for intervention refinement.

Phase II: an intent-to-treat analysis will be used. Generalized linear mixed models will be applied to test for differences between study arms for dichotomous (IPT initiation, IPT completion, HIV testing) and continuous (yield of child contacts, yield of active TB) outcomes. Models will include fixed effects for study arm and patient characteristics, and random effects for study site to adjust for potential non-independence of observations.

Phase III: the analysis of acceptability will be based on grounded theory framework, which encourages the emergence of ideas and theories from within the dataset [36, 39]. This will help to elucidate the complex, social pathways that may impact TB prevention efforts among child contacts. An iterative process to data collection and analysis will be used. All in-depth interview audio-recordings and supplementary and contextual notes will be transcribed verbatim and translated from Sesotho into English. A preliminary review of the first five interview transcripts in each group will be conducted to develop an initial codebook that will be subsequently be applied to the remaining interviews. Dedoose software will be used to manage and code data and facilitate systematic data management. A list of broad codes will be compiled, based on preliminary review of transcripts. Codes deemed relevant for the study aims will be re-applied to the transcripts to allow for active development of themes. Coding results will be regularly assessed for inter-rater reliability in coding and text segmentation. Thematic comparisons within and across narratives will be used to identify latent patterns and negative cases in relation to TB prevention issues. Theoretical notions about the role of caregivers in IPT initiation and adherence will be developed by analyzing the study themes in the context of existing literature and theorizations related to TB treatment initiation and adherence. Data from providers and caregivers will be analyzed separately and comparatively. Data analysis will explore contextual factors related to caregivers’ and providers’ perceptions of acceptability and utilization of intervention components and illuminate common and divergent themes.

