### Facility selection

In collaboration with the MOH, a single district was chosen for conduct of the study in order to enhance internal validity and maximize implementation cost efficiency. Of 19 public health facilities that provide TB services in Berea District, 10 were selected as study sites. The remaining nine health facilities were excluded from the sampling frame because of low TB patient case load (on average, < 6 patients with TB notified per quarter). Both hospitals (*N* = 2) and health centers (*N* = 8) were included to enhance generalizability of study findings as TB services are provided in both types of facility in Lesotho.

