### Assignment to study arm

As this is a cluster-randomized trial, assignment to study arm was done at the health facility level and not at the individual participant level. Ten health facilities (clusters) were randomized to deliver CBI or SOC, following stratification by facility type (hospital or health center). Before randomization, study sites were numbered sequentially within each stratum and intervention status was randomly assigned within each stratum by the Principal Investigator (PI) using SAS v. 9.3 (SAS Institute, Cary, NC, USA). Patients enrolled in health facilities assigned to the SOC arm receive standard of care supported by the Lesotho MOH, whereas those enrolled in health facilities assigned to the CBI arm receive the SOC plus the community-based intervention. Healthcare providers, patients, and study staff are not blinded to the assigned study arm.

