### Sample size and power calculations for phase II

Power calculations were based on the primary outcomes of yield of child contacts and IPT initiation and completion. Based on previous programmatic data from the setting, we anticipated an average of 54 new TB cases per facility per year in Berea District. Based on past experience, the Lesotho TB program estimates that the number of child contacts currently identified per case is 0.5. Thus, at least 27 child contacts are expected to be screened for TB symptoms per SOC facility per year. Based on previous programmatic data, an estimated 5% of contacts will be found to have active TB and fewer than 5% will have contraindications for IPT, resulting in at least 25 child contacts eligible for IPT per facility per year for a total of 75 IPT eligible child contacts per facility over the 3 years of the study. CBI is hypothesized to increase identified child contacts from an average of 0.5 to 2.0 for each adult TB case. Using the two-sided *t* test with a significance level of 0.05 and a standard deviation of 2.5, we will have 91% power to detect a difference of 1.5 between group means. Assuming the two-sided Farrington and Manning score test with α = 0.05 and an intra-cluster correlation coefficient (ICC) of 0.05, we will have between 79% and 98% power to detect a difference in IPT initiation from 20% (SOC) to 40–50% (CBI). This will result in an estimated total of 375–450 child contacts initiating IPT across all sites. Assuming that 20% of child contacts will initiate IPT, 15 child contacts at each clinic will be eligible for IPT completion. Using the two-sided Farrington and Manning score test with α = 0.05 and ICC of 0.05, we will have 83–99% power to detect a difference in IPT completion from 30% (SOC) to 60–70% (CBI).

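### The stated Phase II model leaves out facility type, the factor used to stratify randomization; this costs power, and adding it should go with a test on between-site degrees of freedom

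*Protocol article*

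**What the plan says.** Under Assignment to study arm, the protocol article says that facilities were stratified by type and that "intervention status was randomly assigned within each stratum". Facility selection gives the strata as two hospitals and eight health centers. The number of each type per arm is not stated.

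Under Statistical methods, Phase II outcomes are to be analyzed by generalized linear mixed models, and the terms are listed: "Models will include fixed effects for study arm and patient characteristics, and random effects for study site". No reference distribution, degrees-of-freedom method or small-sample correction is named, and none is ruled out.

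The sample size section uses a two-sided 5% level for the proportions. For IPT initiation at 20% vs 40–50% it states: "an intra-cluster correlation coefficient (ICC) of 0.05, we will have between 79% and 98% power". For completion at 30% vs 60–70% it states 83–99%.

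**The concern.** When randomization is balanced within strata, the stratum contributes equally to both arms and its effect largely cancels from the arm difference. A model without the stratum still counts that effect as unexplained variation between sites. The standard error is then too large for the design actually used, and power is lost.

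The article gives reason to expect hospitals to differ from health centers. Complicated cases are referred to district hospitals, and chest radiographs are done there, which bears on who is found eligible for IPT. With ten sites in all, one atypical site per arm can dominate the error term. The listed model serves all three Phase II primary outcomes.

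**Working it through.** **Inputs from the article.** Ten sites (2 hospitals, 8 health centers); ICC 0.05; two-sided 5% level; 75 eligible contacts per facility for initiation; 15 per facility for completion; rates as above.

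**Assumptions.** Five sites per arm with one hospital each; equal cluster sizes; a hospital gap of 0, 10 or 20 percentage points. The article gives no gap.

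**1. The stated power.** Design effect for initiation: 1 + 74 × 0.05 = 4.7. Effective n per arm: 5 × 75 / 4.7 = 79.8. For 20% vs 40%, the pooled SE is √(2 × 0.3 × 0.7 / 79.8) = 0.0726 and the unpooled SE is √((0.16 + 0.24) / 79.8) = 0.0708. Power = Φ((0.20 − 1.96 × 0.0726) / 0.0708) = 0.793, against the stated 79%. The upper end gives 0.983 (stated 98%). For completion the design effect is 1.7 and effective n is 75 / 1.7 = 44.1. Power is 0.820 (pooled) to 0.844 (unpooled), against 83%; the upper end is 0.975 to 0.984, against 99%. The stated figures therefore follow from a normal-based test with a design effect, with no allowance for having ten clusters.

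**2. The same inputs on a t reference.** Initiation: noncentrality 0.20 / 0.0708 = 2.82; power 0.70 on 8 df (arm only) and 0.68 on 7 df (arm plus facility type). Completion: SE √((0.21 + 0.24) / 44.1) = 0.101; noncentrality 0.30 / 0.101 = 2.97; power 0.74 and 0.72.

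**3. How the omitted stratum enters the error.** The variance of a site proportion is p(1 − p) × 4.7 / 75. Averaged over 20% and 40% this is 0.20 × 0.0627 = 0.0125. With one hospital among five sites, a gap g adds 0.8g² to the residual sum of squares in each arm, so 1.6g² / 8 = 0.2g² to the residual variance.
- g = 0.10 adds 0.002, which is 16%.
- g = 0.20 adds 0.008, which is 64%, so the SE is about √1.64 = 1.28 times too large.

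The true variance of the arm difference is essentially unchanged, because the gap is present in both arms.

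**4. Simulated power, initiation 20% vs 40%.** Site-level linear model, 75 per site, beta-distributed site rates with ICC 0.05, arm averages held fixed.

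| Hospital gap | Arm only, 8 df | Arm + facility type, 7 df |
|---|---|---|
| 0 | 69% | 67% |
| 10 points | 64% | 68% |
| 20 points | 50% | 70% |

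A second simulation gave 70% vs 69%, 62% vs 66% and 47% vs 66% for the same gaps. Under no arm effect, the arm-only test on 8 df rejects about 5% with no gap and between 1% and 4% with gaps of 10 to 20 points. The adjusted test on 7 df stays at about 5%.

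**5. Adding the stratum with a normal reference.** Comparing a 7-df statistic with 1.96 gives 2P(t₇ > 1.96) = 0.091. In a simulated random-intercept logistic model fitted by maximum likelihood (log-OR for hospital 0 or 1.0), type I error was 0.137–0.139 for initiation and 0.071–0.080 for completion. A t₇ reference on that same fit gave 0.072–0.088 and 0.031–0.036, so the df choice alone does not restore 5% there.

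**6. The listed terms with a normal reference.** In the same logistic model for initiation, type I error was 0.116 with no hospital effect and 0.043 with a hospital log-OR of 1.0. In the latter case the median SE was 0.375 against an empirical SD of 0.320.

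**The case against.** The strongest reply is that this is a condensed article. Its sentence on model terms may not be exhaustive, and the analysis plan may add facility type and a small-sample method. For the method of inference this stands: the article is silent, and such detail is commonly left to the analysis plan. A reader might infer that the trial will use large-sample inference, and so that false-positive rates of 11–13% follow. The text does not support that, because it names no Wald test and no df rule. The normal-based power calculation is suggestive but does not fix the analysis.

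For the stratum the reply is weaker. The article does specify the model terms, and a site-level factor does not fall under patient characteristics.

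It is also fair to say that the power loss depends on a gap the article does not give, that the gap would be estimated from only two hospitals, and that the one-per-arm split is assumed. A 10-point gap costs only about 4 points. But the cost of adjusting when there is no gap is smaller still.

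**Conclusion.** The mismatch between the stratified design and the listed model terms is real. Its consequence is a conservative test and lost power: about 4 points for a 10-point hospital gap and about 20 points for a 20-point gap, for initiation at 20% vs 40%. This assumes one hospital per arm and equal cluster sizes.

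A reader might go further and conclude that both the error rate and the precision of the primary analyses are wrong, or that their p-values cannot be trusted. That does not follow. Omitting the stratum alone does not inflate type I error. Inflation needs a large-sample reference, which the article neither adopts nor excludes. The two matters are linked because adding facility type while keeping a normal reference would remove the conservatism and raise type I error.

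The simulations cover the two binary primary outcomes only. No figure is offered for yield of child contacts.

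**What to change.** Add facility type (hospital or health center) as a fixed effect in every Phase II model. In the same change, state that the arm effect is tested on between-site degrees of freedom, 10 − 3 = 7. A two-stage site-level analysis does this and held 5% in the check; patient characteristics can be adjusted for in its first stage. A permutation test restricted to the stratified allocations is an alternative or a confirmation. With one hospital and four health centers per arm there are 2 × 70 = 140 allocations, so the smallest two-sided p is 2 / 140 = 0.014. If the mixed model is kept as primary, its small-sample correction should be named and its type I error checked at ten sites, since a t₇ reference on a maximum-likelihood logistic fit still gave 7–9% for initiation. State the number of hospitals per arm.

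The cost is one degree of freedom, wider intervals, and 1 to 2 points of power if hospitals do not differ. The sample size section should also acknowledge that, on a 7 to 8 df reference, lower-end power is about 67–70% rather than 79% for initiation and about 71–74% rather than 83% for completion. Data collection and trial conduct are unaffected.

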### Monitoring

As this is an implementation science study utilizing the recommended standard of care child TB contact management as per country guidelines rather than an experimental intervention, a data monitoring committee was not deemed necessary. Study personnel were trained to assess study-related adverse events, such as loss of confidentiality, and to notify the PI immediately if they learned of an adverse event. In the event of an adverse event, an incident report will be completed describing the incident, its possible cause, and steps taken to address the adverse event and to prevent its recurrence. The Columbia University Medical Center Institutional Review Board and the Lesotho National Health Research and Ethics Committee will be informed according to their respective reporting guidelines.

Internal monitoring of intervention delivery at each study site is performed weekly by the nurse mentor, to ensure that each site is adhering to study standard operating procedures; in case of non-adherence, the nurse mentor will retrain the providers. In addition, the district TB/HIV coordinator monitors contact tracing and IPT provision for all study sites. External monitoring visits are performed three times per year by the PI and include review of each site’s performance and adherence to confidentiality guidelines.

### Ethics and consent process

The protocol was reviewed and approved by the Columbia University Medical Center Institutional Review Board (Ref AAAN7358) and the Lesotho National Health Research and Ethics Committee (Ref ID78-2015). Protocol modifications are to be submitted to the ethics committees. Both regulatory entities determined the medical record review as eligible for waiver of individual consent for index cases and their child contacts. Healthcare providers and caregivers who participate in the key informant interviews provide written informed consent. Consent forms and all of the identifying information obtained from study participants are stored in separate locked filing cabinets in a locked room. Upon determination of eligibility, participants are assigned unique identification numbers. The study database includes participant unique identification numbers only; no participant names or identifiers are recorded. A master list with each participant’s name and unique identification number is in a locked cabinet, and will be maintained only long enough to permit study investigators to review and audit the data; afterwards, this document will be destroyed, as per standard approaches. Investigators have and will maintain access to the full trial dataset.

The trial design and protocol adhere to Standard Protocol items: Recommendations for Interventional Trials (SPIRIT) criteria (www.spirit-statement.org); see the SPIRIT figure (Fig. 1). The SPIRIT checklist can be found as Additional file 1: Table S1.

**Fig. 1 Fig1:**
[figure not shown]
Schedule of study interventions and assessments

### Dissemination

A dissemination strategy was developed to ensure that study findings are shared with key stakeholders, regardless of the magnitude or direction of effect. This strategy includes a dissemination meeting in Lesotho with the MOH, District Health Management Team, healthcare providers, and patients from participating health facilities; a dissemination report for the MOH; dissemination of findings through the WHO Childhood TB subgroup; presentations at scientific conferences; and publications in peer-reviewed journals. Investigators will adhere to recommendations from the International Committee of Medical Journal Editors regarding authorship. Data, which have been stripped of all identifiers, will be made publicly available following the publication of primary and secondary outcome papers in accordance with the National Institutes of Health Data Sharing Policy [40].

